### Randomisation

Central randomisation software will be used with stratification by site and baseline glycated haemoglobin. The randomisation ratio will be 1:1 within each stratum. The randomisation list created by the study statistician is encrypted.

### Treatment period

#### Automated day-and-night hybrid closed-loop insulin delivery combined with low-glucose suspend feature (interventional arm)

Participants allocated to the closed-loop group will be trained on using the study insulin pump (modified Medtronic 640G pump, Medtronic, Northridge, CA, USA) and real-time continuous glucose sensor (Guardian 3, Medtronic). This represents a complex intervention over usual care, especially for subjects under pump therapy alone. Once deemed competent with the use of the devices, participants will receive training required for the closed-loop system. Competency on the use of closed-loop will be evaluated. During closed-loop period, participants will programme meal boluses estimating ingested carbohydrate amounts. Specific instructions during closed-loop related to exercise management, sick day rules, hypoglycaemia and hyperglycaemia management and technical troubleshooting will be provided.

#### Usual care (conventional or sensor-augmented pump therapy) (control arm)

Participants in control arm will receive refresher training on key aspects of insulin pump therapy (advanced boluses, temporary basal, infusion set change, sensor calibrations). During 6-month control intervention period, subjects will continue using either their own insulin pump alone or combined with their prestudy glucose monitoring device.

At the study initiation visit, participants in both study groups will be fitted with a blinded continuous glucose monitoring system (Libre Pro) that will be worn for up to 14 days. If the sensor fails or gets detached, another sensor may be inserted. The sensor data may be used to optimise insulin delivery.

### Assessments at 3 and 6 months

A blood sample will be collected for measurement of glycated haemoglobin. A urine pregnancy test in females of childbearing potential will be performed. As per usual clinical practice, glucometer downloads and pump data will be reviewed, and adjustments to insulin pump settings will be made as required. Validated surveys evaluating the impact of the devices employed on quality of life, psychosocial and cognitive functioning, diabetes management and treatment satisfaction will be administered. At the 3-month follow-up visit, participants in both study groups will be fitted with blinded continuous glucose monitoring systems (Libre Pro). For assessment of glycaemic control during the final 3-month period of the trial, participants in both study groups will be fitted with a blinded continuous glucose monitoring system 2–4 weeks before the end of study. At the 6-month visit, the same procedures as at the 3-month visit will be followed. A subset of subjects/guardians will be invited to join follow-up focus groups.

### Study contacts during 6-month study period

Participants in the two study groups will have an equal number of contact visits. The first planned contact will occur within 24–48 hours after study initiation visit. During the first 2 weeks of the study period, participants will be contacted weekly. Thereafter, participants will be contacted monthly. Subjects/parents and/or the clinical team are free to adjust insulin therapy, but no active treatment optimisation will be undertaken by the research team.

### Devices download

As per usual care, insulin pump and blood glucose meter will be downloaded (Medtronic CareLink) every clinic visit (at least every 3 months).

### Closed-loop system

The FlorenceM closed-loop system (figure 2) incorporates a computer-based algorithm hosted by an Android smartphone, which interacts wirelessly with the modified investigational-use-only 640G pump through a proprietary translator device included in the smartphone’s enclosure. By using the information received from the glucose sensor, every 10 min the system computes a new temporary basal insulin infusion rate, which is automatically sent to the insulin pump. The treat-to-target control algorithm aims to achieve a default glucose level of 5.8 mmol/L (104 mg/dL) and regulates the actual level depending on fasting versus postprandial status and the accuracy of model-based glucose predictions. No remote monitoring is planned. While the system is charging and connected to internet, the device uploads data on a server. The study pump comprises continuous glucose monitoring receiver and provides hypoglycaemia and hyperglycaemia alarms, which can be activated/personalised by the participants.

**Figure 2 F2:**
[figure not shown]
FlorenceM closed-loop system prototype. The system consists of a continuous glucose monitoring transmitter with Guardian 3 sensor (Medtronic), an insulin pump (modified 640G pump, Medtronic) and an Android smartphone running the control algorithm (Cambridge).

### Safety precautions during closed-loop

Participants will be asked to perform capillary calibrations before breakfast and dinner. If sensor glucose value is >3.0 mmol/L (54 mg/dL) different from capillary glucose level, the sensor will be recalibrated. These directions are based on an in silico simulation of hypoglycaemia and hyperglycaemia risk using the validated Cambridge simulator.^29^ If sensor glucose becomes unavailable or the smartphone is not in range/operational, the pump will automatically deliver the preprogrammed insulin as set on the pump within 30 min. Safety rules limit maximum insulin infusion and suspend insulin delivery when sensor glucose is ≤4.3 mmol/L (77 mg/dL) or when glucose is rapidly decreasing. In case of a communication failure between control algorithm device and the study pump, the low-glucose feature will interrupt insulin delivery, provided sensor glucose is available. Low-glucose suspend/predictive low-glucose management will be initially set to suspend insulin delivery at sensor glucose values of 3.9 mmol/L (70 mg/dL) or less, after which the setting could range from 2.8 to 5.0 mmol/L (50–90 mg/dL). Predictive low-glucose suspend will not be used. Insulin delivery will be resumed in accordance of the low-glucose suspend feature implemented on the study pump. A 24-hour local telephone helpline will be available for any technical device issues or problems related to diabetes management.

### Participant withdrawal criteria

The following prerandomisation withdrawal criteria will apply:Subject/caregiver is unable to demonstrate safe use of study insulin pump as judged by the investigator.Subject/caregiver fails to demonstrate compliance with insulin pump and capillary self-monitoring of blood glucose during run-in.

Prerandomisation and postrandomisation withdrawal criteria will comprise:Subjects/caregivers may terminate participation in the study at any time without necessarily giving a reason and without any personal disadvantage.Significant protocol violation or non-compliance.Two distinct episodes of severe hypoglycaemia.Two distinct episodes of diabetic ketoacidosis unrelated to infusion site failure and related to the use of the closed-loop.Decision by the investigator or the sponsor that termination is in the subject’s best medical interest.Allergic reaction to insulin.Allergic reaction to adhesive surface of infusion set or glucose sensor.Subject becomes pregnant during the study period.

Subjects withdrawn due to reasons 4–10 will be invited to provide blood sample at the end of the planned study intervention for the assessment of glycated haemoglobin.

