### Statistical analysis

#### Primary outcome analysis

The primary analysis will follow the intention-to-treat principle. Data from all randomised subjects will be analysed in the group to which the subjects were assigned through randomisation regardless of the actual treatment received. Data will not be truncated due to protocol deviations.

The primary analysis will evaluate between group differences in glycated haemoglobin levels at the end of treatment period. A 5% significance level will be considered statistically significant for the primary outcome comparison.

Mean±SD values or percentiles appropriate to the distribution will be reported for the primary outcome by treatment group. The two treatment groups will be compared using a linear regression model adjusting for glycated haemoglobin at baseline, age and clinical centre as random effect. A 95% CI will be reported for the difference between the randomisation groups based on the linear regression model. Residual values will be examined for an approximate normal distribution. If values are highly skewed, then a transformation or robust statistical methods (eg, non-parametric or MM estimation) will be used instead. A detailed analysis plan will be provided separately.

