#### Other key endpoints

For the following key endpoints at 6 months, the familywise type I error rate will be controlled at two-sided α=0.05. A gatekeeping strategy will be used, where the primary endpoint will be tested first, if passing the significance testing, other key endpoints will be tested in the order listed below using the fixed-sequence method at α=0.05.Time spent in the target glucose range from 3.9 to 10.0 mmol/L (70–180 mg/dL).Mean sensor glucose.Time spent above target glucose 10.0 mmol/L (180 mg/dL).Time spent below target glucose 3.9 mmol/L (70 mg/dL).

If a non-significant (p>0.05) result is obtained for any outcome on this list, no further hypothesis testing will be performed for any metrics further down on the list.

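### After withdrawal for non-compliance only an HbA1c sample is sought, so the four key sensor endpoints at 6 months can lose randomised participants

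*Protocol article*

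**What the plan says.** Under Participant withdrawal criteria, the second list opens with "Prerandomisation and postrandomisation withdrawal criteria will comprise" and includes "Significant protocol violation or non-compliance". Counting the two prerandomisation items first, this is reason 4 of 10. It is not restricted to one arm, and no threshold is given. On what happens next, the section says: "Subjects withdrawn due to reasons 4–10 will be invited to provide blood sample at the end of the planned study intervention". The sample is for HbA1c; no sensor wear is mentioned.

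Under Primary outcome analysis: "Data from all randomised subjects will be analysed in the group to which the subjects were assigned through randomisation regardless of the actual treatment received", and "Data will not be truncated due to protocol deviations".

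Under Other key endpoints: "For the following key endpoints at 6 months, the familywise type I error rate will be controlled at two-sided α=0.05". The four endpoints are time in range, mean sensor glucose, time above range and time below range, tested in that fixed order after HbA1c. The closing sentence of Insulin and other endpoints bases the glycaemic metrics on blinded sensor wear after randomisation. Tables 1 and 2 place that wear at visits 4, 6 and 7, with visit 7 falling 2–4 weeks before visit 8.

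**The concern.** The protocol foresees that withdrawal would cost it the primary outcome and arranges to recover HbA1c. It makes no matching arrangement for the four endpoints next in the testing hierarchy. A participant who leaves for non-compliance before visit 7 therefore has no planned sensor value for the period those endpoints describe. This differs from a gap in the analysis plan: a plan can model a missing value but cannot recover a sensor that was never fitted.

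The loss is unlikely to be random, because people withdrawn for non-compliance probably have worse glucose control than those who stay. It may also be unequal between arms. The trial is open-label, the criterion leaves room for judgement, and the closed-loop arm must learn a new pump, sensor and algorithm while controls keep their own equipment. If more poor adherers left the closed-loop arm, the comparison of those observed would favour closed-loop on endpoints meant to carry confirmatory weight.

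**Working it through.** **1. The plan's own figure.** Inputs from Power calculation: difference 0.4%, effective SD 0.71%, two-sided 5%, power 85%, 1:1 allocation.

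- Normal approximation: n per arm = 2 × (1.960 + 1.036)² × 0.71² / 0.4² = 56.6, so 57 per arm and 114 in total.
- t-based: 57.55, so 58 per arm and 116 in total, as stated.
- Inflation: 116 × 1.10 = 127.6, which gives the stated figure of about 128 (64 per arm). Dividing instead, 116 / 0.90 = 128.9, or 129.

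The sample size is not in dispute. It supplies the 64 per arm used below and shows that the plan allows 10% for dropout and non-compliance together.

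**2. What a withdrawn participant contributes.**

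| Withdrawn for reason 4 | Blinded sensor wear after randomisation | End-of-study HbA1c |
|---|---|---|
| between visits 4 and 6 | visit 4 only | invited |
| between visits 6 and 7 | visits 4 and 6 | invited |
| after the visit 7 wear | visits 4, 6 and 7 | invited |

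In the first two rows there is no end-of-study sensor value.

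**3. Size, by illustration.** These assumptions are not in the article: 64 randomised per arm; a fraction f of the closed-loop arm lost and no controls lost; only observed end-of-study values analysed; equal SD of 1 in both arms.

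*Overstated effect.* If those lost gain nothing, the all-randomised effect is (1 − f) times the effect in those retained. The observed effect is therefore too large by 1/(1 − f) − 1. At f = 0.10 this is 1/0.90 − 1 = 11.1%.

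*Type I error.* Suppose there is no true effect in all randomised and those lost are D SD worse than those retained. The observed closed-loop mean then shifts by f × D, with SE = √(1/(64(1 − f)) + 1/64). The two-sided error is Φ(−1.960 + fD/SE) + Φ(−1.960 − fD/SE). At f = 0.10, SE = √(1/57.6 + 1/64) = 0.1816.

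- D = 0.5: fD/SE = 0.05/0.1816 = 0.275; error = 0.0460 + 0.0127 = 0.0587.
- D = 1.0: fD/SE = 0.10/0.1816 = 0.551; error = 0.0794 + 0.0060 = 0.0854.

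| f | Lost of 64 | Effect overstated by | Error, D = 0.5 | Error, D = 1.0 |
|---|---|---|---|---|
| 2% | 1.3 | 2.0% | 5.04% | 5.15% |
| 5% | 3.2 | 5.3% | 5.22% | 5.90% |
| 10% | 6.4 | 11.1% | 5.87% | 8.54% |
| 15% | 9.6 | 17.6% | 6.92% | 12.86% |

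**4. The gate.** These are single-test rates. Sensor endpoints are tested only after HbA1c is significant. If closed-loop affects nothing, the HbA1c test caps the familywise error. The tabulated rates apply in full only if HbA1c truly improves while the sensor endpoint does not, an unlikely combination. The overstated estimate is therefore the more practical worry.

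**The case against.** Several stronger readings are tempting, and the article does not support them.

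- *That the withdrawal criterion contradicts intention-to-treat.* The analysis rule governs how collected data are analysed. The withdrawal section governs who leaves. Nothing drops withdrawn participants from the main analysis, and exactly this group is asked back for the primary outcome. For the sensor endpoints the aim is undermined, not contradicted.
- *That low users of closed-loop are removed.* Non-compliance is not tied to closed-loop use and the criterion covers both arms; controls also have visits, sensor wear and glucose testing to comply with. Perprotocol analysis lists not having withdrawn and 70% closed-loop use as separate conditions, which implies that some low users stay in the trial and in the main analysis.
- *That a withdrawn participant has no sensor data at all.* Wear at visits 4 and 6 may already exist, no text discards it, and the article refers to wear periods in the plural. The separate analysis plan may say how earlier wear and missing values are used. Even so, earlier wear is not the final wear, and the endpoints are specified at 6 months.
- *That the error rate could reach 15%.* This needs 10% lost from one arm only, those lost 20 points lower in time in range with an SD of 12 (20/12 = 1.67 SD), 60 per arm, and no gate. It is too extreme to rest on.

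One further point stands: greater loss in the closed-loop arm is an inference. The 10% allowance amounts to 128 − 116 = 12 participants over both arms and all causes. Losing 6.4 from one arm for this kind of reason is already a pessimistic case.

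**Conclusion.** The point holds as a limited gap in data collection. As written, a participant in either arm withdrawn for non-compliance before visit 7 has no end-of-study value on any of the four familywise-controlled sensor endpoints, while HbA1c is largely protected. How much this matters depends on how many are withdrawn, how unevenly, and how different they are; the article gives none of these. At 2% loss from one arm the effect is negligible. At 10% from the closed-loop arm only, the treatment effect would be overstated by about 11% under zero gain in those lost. The single-test error would be about 5.9% to 8.5% under a null sensor effect with the HbA1c gate passed. Equal losses of similar participants in both arms would largely cancel. The change is worth making because it is small and protects confirmatory endpoints. The gap does not threaten the primary analysis.

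**What to change.** In Participant withdrawal criteria, separate stopping study treatment from stopping follow-up, and widen the existing invitation. For example:

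> *Participants in either arm to whom any of reasons 4–10 applies will be invited, where they agree, to complete the remaining scheduled outcome assessments, in particular the visit 7 blinded sensor wear and the final HbA1c sample. These data will be analysed in the randomised group for the primary and the four key endpoints.*

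Then reconcile that section with Primary outcome analysis and Other key endpoints, so that all three describe the same follow-up and the same population. The blinded sensor is separate from the closed-loop system and its wear is already scheduled, so collecting it does not depend on continued closed-loop use.

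The cost is an amendment, which under Ethics and dissemination needs ethics and regulatory approval first if it is substantial, plus some effort to retain less engaged families. Enrolment began in June 2017 and follow-up was expected to end by January 2020, so the change helps only participants who have not yet passed visit 7. When study treatment should stop is a clinical matter and is not addressed here.

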### Safety analyses

The following events will be recorded and compared between treatment groups:Number of severe hypoglycaemia events per subject and incidence rate per 100 person-years.Number of diabetic ketoacidosis events per subject and incidence rate per 100 person-years.Sensor glucose-measured hypoglycaemic events per week (>15 min with glucose <3 mmol/L, 54 mg/dL).Sensor glucose-measured hyperglycaemic events per week (>15 min with glucose >16.7 mmol/L, 300 mg/dL).Proportion of subjects with worsening of glycated haemoglobin from baseline to 6 months by >0.5%.

If we record enough observed events to allow formal statistical modelling for above safety outcomes, we will perform the following analyses. Poisson regression models will be constructed to compare the treatment group difference for event rates by adjusting for age, baseline glycated haemoglobin and random site effect. If any outlier exists, a robust Poisson regression model will be used instead. For binary glycated haemoglobin outcome, logistic regression models will be used to compare the treatment group difference by adjusting for age, baseline glycated haemoglobin and random site effect.

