### Perprotocol analysis

We will conduct a perprotocol analysis in order to replicate the primary analysis, but limited to participants who did not withdraw from the study (withdrawals excluded even if they return for a 6-month glycated haemoglobin measurement) and used closed-loop for at least 70% of the time (intervention group).

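### Withdrawal for repeated severe hypoglycaemia or closed-loop-related ketoacidosis can end observation of those same safety outcomes, for ketoacidosis in one arm only, with only an HbA1c named afterwards

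*Protocol article*

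**What the plan says.** The Participant withdrawal criteria section lists two criteria that apply before randomisation, then eight that apply before and after it. Among the eight are "Two distinct episodes of severe hypoglycaemia", with no restriction to an arm, and "Two distinct episodes of diabetic ketoacidosis unrelated to infusion site failure and related to the use of the closed-loop". On what follows, the section states: "Subjects withdrawn due to reasons 4–10 will be invited to provide blood sample at the end of the planned study intervention", the sample being for HbA1c. The Perprotocol analysis section mentions the same single return: "withdrawals excluded even if they return for a 6-month glycated haemoglobin measurement".

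The Safety analyses section compares between arms "Number of severe hypoglycaemia events per subject and incidence rate per 100 person-years" and "Number of diabetic ketoacidosis events per subject and incidence rate per 100 person-years", and also "Sensor glucose-measured hypoglycaemic events per week". Time below 3.9 mmol/L at 6 months is the last of the other key endpoints in the fixed test sequence. Sensor metrics come from blinded wear after randomisation, which Tables 1 and 2 place at visits 4, 6 and 7. The wear 2–4 weeks before the end of study is the one assigned to glycaemic control in the final three months.

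**The concern.** Two events that the trial compares between arms are also reasons to leave the trial. Once a child is withdrawn for them, nothing in the article keeps event reporting or sensor wear going. Loss of follow-up then depends on the outcome, and for ketoacidosis it depends on arm as well, through a causality judgement made in an open-label trial. For a usual-care child with two severe hypoglycaemia episodes there is no study device to stop, so leaving the study only loses data.

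Safety is a stated aim. Severe events are likely to be few, and one child with recurrent events can then make up a large share of an arm's total. The final sensor wear may also be missing for children whose reason for leaving was hypoglycaemia, and that wear bears on time below 3.9 mmol/L. An analysis plan cannot recover data that were never collected.

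**Working it through.** **1. Which reasons lead to which follow-up.** Numbering the two lists in order, the pre-randomisation criteria are 1 and 2, voluntary withdrawal is 3, protocol violation 4, severe hypoglycaemia 5, ketoacidosis 6, and pregnancy is 10. Reasons 5 and 6 fall within 4–10, so the HbA1c invitation covers them.

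**2. Other places that might extend follow-up.** The Ethics and dissemination section refers to operating procedures for adverse event reporting. The Data Safety Monitoring Board section requires notification of serious adverse events. Neither says that withdrawn participants continue to be followed. The intention-to-treat statement stands under the primary outcome, and post-withdrawal collection supports it for HbA1c only.

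**3. Arm dependence.** The ketoacidosis criterion needs a link to closed-loop use. Usual-care participants have no study closed-loop, and current use of any such system is an exclusion. The severe hypoglycaemia criterion applies to both arms.

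**4. Size.** The article gives no event rate and no expected number of withdrawals, so there is no figure of its own to reproduce. The inputs are:
- From the article: 64 per arm (Power calculation); T = 7/12 year from randomisation to visit 8 (Tables 1 and 2); exclusion of children with more than one severe hypoglycaemia episode, or more than one ketoacidosis episode, in the previous 6 months (Box 1).
- Assumed: mean rates of 10 and 30 events per 100 person-years; either one common rate or gamma-distributed rates between children (shape 0.05–0.3, smaller meaning more uneven); the same rate after withdrawal as before; every second event triggers withdrawal.

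*Common rate λ, with m = λT.* The probability of two or more events is 1 − e^(−m)(1 + m). The expected number of events lost per child is m − [2 − e^(−m)(2 + m)].
- λ = 0.10: m = 0.0583; probability 0.0016, so 64 × 0.0016 = 0.10 children per arm; 0.002 events lost per arm.
- λ = 0.30: m = 0.175; probability 0.0136, so 64 × 0.0136 = 0.87 children per arm; 0.05 events lost per arm.

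Here expected events divided by expected person-time equals λ exactly, so the pooled rate is essentially unbiased despite the stopping rule.

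*Uneven rates.* Simulation of 6,000,000 children per scenario, first removing those with more than one event in a simulated prior 6 months, then stopping at the second event:

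| Mean rate before exclusion | Shape | True rate after exclusion | Observed rate | Children per 64 with two events | Events lost per 64 | Events lost, % |
|---|---|---|---|---|---|---|
| 10 | 0.3 | 9.8 | 9.7 | 0.34 | 0.05 | 1.3 |
| 10 | 0.2 | 9.5 | 9.3 | 0.41 | 0.08 | 2.2 |
| 10 | 0.1 | 8.8 | 8.4 | 0.51 | 0.16 | 4.8 |
| 10 | 0.05 | 7.4 | 6.8 | 0.52 | 0.24 | 8.8 |
| 30 | 0.3 | 26.1 | 24.8 | 1.67 | 0.58 | 5.9 |
| 30 | 0.2 | 23.9 | 22.2 | 1.67 | 0.71 | 8.0 |
| 30 | 0.1 | 18.9 | 16.8 | 1.46 | 0.85 | 12.0 |
| 30 | 0.05 | 12.9 | 11.0 | 1.05 | 0.76 | 15.6 |

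Rates are per 100 person-years. For ketoacidosis these figures are upper limits at the given rate, because only episodes that meet the criterion count towards withdrawal.

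**5. Sensor data.** A child withdrawn between visits 4 and 6 keeps the visit 4 wear and loses the wears of visits 6 and 7. One withdrawn between visits 6 and 7 loses the last wear only.

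**The case against.** The strongest reply is that the article is a condensed text. It does not say that event follow-up stops, and the full protocol or the adverse event procedures may continue it. That remains possible. But the article does state what is asked of withdrawn participants, and in both places it names HbA1c alone. This is therefore a stated rule that needs correcting or clarifying, not a detail merely left out.

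The other objections concern size and direction, and they largely stand.
- **Size.** Without the Box 1 exclusion, the same model loses 1–14% of events at 10 per 100 person-years and 8–38% at 30. The exclusion removes much of the tail that drives those figures.
- **Direction.** A reader might infer that the rules lower the closed-loop event rate and so favour closed-loop. The documents do not support this. The rate uses person-years, so withdrawn children also leave the denominator, and the hypoglycaemia rule acts in both arms. A child withdrawn for closed-loop-related ketoacidosis would presumably be off the device, so added follow-up could move that arm's rate either way.
- **Ketoacidosis count.** A reader might infer that every closed-loop child stops being counted at two episodes while usual-care children go on accruing them. Episodes due to a failed infusion site, or not related to closed-loop, do not trigger the rule. A usual-care child can also be withdrawn by decision of the investigator or sponsor.
- **Sensor data.** Wear before withdrawal is kept, and it is an assumption that two severe episodes mark the children with most sensor hypoglycaemia.

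Formal modelling of events is also conditional on there being enough of them.

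**Conclusion.** The point holds as a moderate weakness in safety data collection. As the article stands, observation of severe hypoglycaemia can end because of severe hypoglycaemia in either arm, and observation of ketoacidosis can end because of closed-loop-related ketoacidosis in one arm. No event or sensor follow-up is named afterwards.

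The effect is probably small: about 0.3–0.5 children per arm reaching two events at an assumed 10 per 100 person-years and 1.1–1.7 at 30, with fewer than one event per arm lost. The count per participant is truncated whatever the distribution of risk. The person-time rate is biased only if risk differs between children; in the scenarios shown it is then about 1% too low (9.7 against 9.8) to 15% too low (11.0 against 12.9). These figures rest on assumed rates and shapes and on an unchanged rate after withdrawal. Neither a bias in favour of closed-loop nor a complete loss of sensor data is shown. The primary HbA1c comparison is not threatened, since HbA1c is the one assessment still sought.

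**What to change.** Leave the clinical stopping criteria unchanged, and separate stopping study treatment from ending follow-up. Invite participants in both arms who meet reasons 4–10 to continue reporting severe hypoglycaemia, ketoacidosis and serious adverse events to month 7, and to wear the visit 7 blinded sensor, in addition to giving the HbA1c sample. Analyse events from randomisation to month 7 by assigned arm. If the full protocol already provides this, a sentence saying so is enough.

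The cost is a short amendment and a small added burden for perhaps 0–2 children per arm under these two criteria, plus any others withdrawn for reasons 4–10. The contacts, visits and sensors are already scheduled in Tables 1 and 2. Participants who choose to leave remain free to do so.

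### The end-of-study HbA1c invitation leaves out participants who withdraw by their own choice, although the primary analysis is meant to include everyone randomised

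*Protocol article*

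**What the plan says.** The section Participant withdrawal criteria has two lists. The first is introduced by "The following prerandomisation withdrawal criteria will apply" and has two entries. The second is introduced by "Prerandomisation and postrandomisation withdrawal criteria will comprise" and has eight. Its first entry reads: "Subjects/caregivers may terminate participation in the study at any time without necessarily giving a reason". The section closes with the collection rule: "Subjects withdrawn due to reasons 4–10 will be invited to provide blood sample at the end of the planned study intervention", so that HbA1c can be assessed.

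Under Primary outcome analysis the article says: "Data from all randomised subjects will be analysed in the group to which the subjects were assigned through randomisation". The endpoint is fixed in the same place: "The primary analysis will evaluate between group differences in glycated haemoglobin levels at the end of treatment period". The comparison uses a "linear regression model adjusting for glycated haemoglobin at baseline, age and clinical centre as random effect".

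Under Perprotocol analysis, participants who withdrew are excluded from that analysis even when a 6-month HbA1c exists for them. No comparable exclusion is stated for the primary analysis.

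**The concern.** The plan intends withdrawn participants to count in the primary analysis, and it takes a deliberate step to obtain their outcome. That step stops short of one group, the families who decide for themselves to leave. Followed as written, the rule does not seek the primary outcome from them.

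This matters because allocation is known. The closed-loop arm has to learn a new pump, a real-time sensor and the closed-loop system, which the article itself describes as complex compared with usual care. The control arm continues with its own equipment. The reasons for leaving, and the number who leave, may therefore differ between arms, and leavers may differ from stayers in HbA1c. If both happen, a comparison of those with a 6-month value is biased. A later analysis plan can model the missing values but cannot recover a sample that was never requested.

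**Working it through.** **Which reason is left out.** The printed item numbers are not visible in the text, so the entries are counted in order.

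- Reasons 1–2: the two entries labelled as applying before randomisation only. As labelled, they do not concern the randomised set.
- Reason 3: voluntary termination by the participant or caregiver.
- Reasons 4–10: protocol violation or non-compliance, severe hypoglycaemia, ketoacidosis, investigator or sponsor decision, insulin allergy, adhesive allergy, pregnancy.

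The count is 2 + 8 = 10, which matches the upper end of the stated range 4–10. Of the eight reasons that can apply after randomisation, seven are invited and one, reason 3, is not.

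**Is there another route to the outcome?** Tables 1 and 2 place the 3-month HbA1c at visit 6, four months after randomisation, and the final HbA1c at visit 8, seven months after randomisation. A voluntary leaver before visit 6 has no scheduled HbA1c after randomisation. One who leaves later has the 3-month value only. No other section provides for a 6-month sample from these participants.

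**The plan's own sample size, and power.** Inputs from Power calculation: effect 0.4, effective SD 0.71, two-sided 5%, power 85%, 1:1 allocation.

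- Normal approximation: n per arm = 2 × (1.960 + 1.036)² × 0.71² / 0.4² = 56.6, so 57 per arm and 114 in total.
- Two-sample t-test: 57.55, so 58 per arm and 116 in total, which is the stated figure.
- Dropout: 116 × 1.10 = 127.6, so 128, as stated (116 / 0.90 would give 129).

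Power with 128 randomised, by share without an outcome (normal approximation):

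| Missing | 0% | 2% | 5% | 10% | 15% | 20% |
|---|---|---|---|---|---|---|
| Power | 89.0% | 88.4% | 87.4% | 85.6% | 83.6% | 81.3% |

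Up to the planned 10%, precision is protected. The sample size is not at fault here.

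**Bias.** In an arm where a share p leaves and leavers' 6-month HbA1c would be higher than stayers' by g, the mean of the stayers is too low by p × g. The complete-case difference between arms is therefore off by p(closed-loop) × g(closed-loop) − p(control) × g(control). If g is the same in both arms this becomes d × g, where d is the difference in the share lost.

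The documents give neither d nor g. Assumed ranges are d = 2, 5 and 10 percentage points and g = 0.25, 0.5 and 1.0 HbA1c percentage points, where g is the gap left after adjustment for baseline HbA1c and age. Entries are d × g, with d × g / 0.4 in brackets:

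| d | g = 0.25 | g = 0.5 | g = 1.0 |
|---|---|---|---|
| 2 points | 0.005 (1%) | 0.010 (2.5%) | 0.020 (5%) |
| 5 points | 0.0125 (3%) | 0.025 (6%) | 0.050 (12.5%) |
| 10 points | 0.025 (6%) | 0.050 (12.5%) | 0.100 (25%) |

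The bottom right corner is demanding. A gap of 1.0 is 1.0 / 0.71 = 1.4 effective SDs. A 10-point difference, such as 15% against 5%, averages 10% and so assigns the whole dropout and non-compliance allowance to voluntary leaving.

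**The case against.** The article says who will be invited; it forbids nobody else. The per-protocol section speaks of withdrawn participants who come back for a 6-month HbA1c without limiting the reason. Reason 3 is also worded as leaving the study, not only the treatment, and not re-approaching children and caregivers who use that right is a defensible choice. Some leavers would decline whatever the rule says.

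Much of this stands. It rules out calling the omission a prohibition, and it shows that some loss is unavoidable. It does not explain why voluntary leavers should not be asked. An invitation can be declined and puts no one at a disadvantage.

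A reader might also infer more than the documents support:

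- That intention-to-treat cannot be achieved. The article promises analysis by assigned group, not complete outcomes, and it defers detail to a separate analysis plan, where the handling of missing values belongs.
- That sensor wear and safety events are not followed after withdrawal. A condensed article need not describe this, and it refers to procedures for adverse event reporting. Its silence is not a finding.
- That safety follow-up is shortened in one arm only. The ketoacidosis reason is tied to closed-loop use, but most of the other reasons, voluntary leaving among them, can arise in either arm.
- That the bias is large. Figures of 0.05–0.10 points arise only towards the upper end of the assumed ranges.

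**Conclusion.** The point holds as a gap in a stated collection rule. Voluntary termination is the one reason labelled as possible after randomisation for which no end-of-study HbA1c is sought, while the primary analysis is defined on all randomised participants. The result is avoidable missing primary-outcome data that may differ by arm.

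The plausible size runs from negligible to moderate: about 0.005–0.10 HbA1c points, or 1–25% of the 0.4-point design effect. That range rests entirely on assumed differences in loss and in outcome, on the same leaver–stayer gap in both arms, and on a complete-case analysis. The direction is not known. If leavers do worse, heavier loss from the closed-loop arm would flatter closed-loop, and heavier loss from the control arm would understate its benefit. Power is not the issue. This is a cheap improvement, not a flaw that invalidates the design.

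**What to change.** Replace the range of reasons in the closing sentence of Participant withdrawal criteria with a rule for every randomised participant who stops for any reason, including the family's own decision. Each is invited to give an HbA1c sample at the planned visit 8 date, or to permit use of a routine clinic HbA1c from that window, unless they refuse further contact or data use. Wording it as any reason also removes the dependence on item numbers.

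The cost is a one-sentence amendment, a line in the withdrawal form and a few extra samples. Even if the whole allowance of 128 − 116 = 12 participants left voluntarily, that would be about 12 samples. Some leavers will still decline, so the change reduces the missing data without eliminating it. The required sample size does not change.
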